## Methods/design

### Study design

The study is a prospective randomized controlled trial comparing the effectiveness of a face-to-face structured patient-specific smoking cessation program conducted by trained ambulatory pharmacists versus brief unstructured pharmacist-delivered advice on smoking cessation rates.

### Study sites

The study is implemented in eight public and private ambulatory pharmacies in the State of Qatar. These pharmacies are located within large ambulatory clinics that serve a large proportion of the Qatar population. To prevent cross contamination with the study, none of these clinics has established smoking cessation programs. Each study pharmacy is staffed by at least three pharmacists. Two pharmacists from each pharmacy are invited to participate in the study. The study is taking place in a semiprivate area in the pharmacy. This area is secluded enough to ensure adequate patient confidentiality.

### Study pharmacists’ training

Prior to starting the study, each study site pharmacist was sent a copy of the study methodology along with a written literature review on smoking cessation and asked to study the material.

Two to three weeks after receipt of the material, the study pharmacist attended a 2-day (8 h/day) smoking cessation training workshop that was organized by the Hamad Medical Corporation (HMC) smoking cessation clinic team and Qatar University (QU) College of Pharmacy.

The training team consisted of [name] [name] (Public Health and Disease Control Consultant and HMC smoking cessation clinic head), [name] [name] (Study Principal Investigator/Assistant Professor and CPP Chair at QU College of Pharmacy), [name] (Associate Professor and CPPD coordinator at QU College of Pharmacy) and [name] [name] [Deputy Dean (Academic Affairs) in Kulliyyahof Pharmacy at the International Islamic University Malaysia (IIUM)]. [name] is considered an international authority in the area of substance abuse, including cigarette smoking.

The HMC smoking cessation clinic is one of the smoking cessation facilities in Qatar. The clinic is run by highly qualified smoking cessation consultants and has a smoking cessation success rate of 40%. In addition to offering smoking cessation treatment, this clinic contributes to community education on the dangers of smoking among the citizens and residents of Qatar and provides smoking-related lectures and seminars for all age groups in the state [36].

The general objective of this workshop is to provide the study pharmacists with enough smoking cessation knowledge and the necessary skills and tools to assess and treat smokers. A smoking cessation training manual that was developed by the study training team is extensively used in the workshop. This manual is also used as an on-site resource by the study pharmacists in their smoking cessation program.

The workshop covered the following: smoking epidemiology and risks, benefits of quitting, a transtheoretical model for behavior change as applied to smoking cessation, the necessary elements for documentation in the patient smoking cessation profile, behavioral modification techniques, classification of smokers according to their stage of change (5 stages: precontemplation, contemplation, preparation, action and maintenance), nicotine replacement therapy (NRT: nicotine patch, lozenge and gum), patient counseling techniques, development of a personalized action plan, use of the exhaled carbon monoxide test, detailed instructions on the program methodology and other needed elements.

In addition, the pharmacists’ training workshop included training the pharmacists on how to follow the study protocol exactly. The study team walked the pharmacists through the study protocol including how to randomly allocate participants to the intervention and control groups, how to deliver the intervention and how to deal with control patients.

During the training workshops, emphasis was also placed on the importance of behavioral and lifestyle modifications. Pharmacists were instructed to encourage smokers who are anticipating quitting to identify the situations that may increase their risk of smoking such as having smokers within the household or at the workplace as well as getting into stressful situations. After identifying these situations, the pharmacists were provided with information they could give to smokers about strategies to improve coping including lifestyle changes to decrease stress and improve QoL, removing visual cues for smoking and staying away from these situations that normally make patients want to smoke [37]. In addition, the pharmacists were trained to provide the smokers with information about what to expect during quit attempts and to address any individual concerns that the smokers may have [38]. Furthermore, they were advised to encourage the smokers to notify family and friends of the plan to quit and to ask for their support [37].

Participant counseling and interviewing techniques were also part of the training workshops. To enhance learning, the pharmacists applied these techniques using patient role-plays in small groups. Topics that were reviewed included counseling skills, verbal and nonverbal communication skills including use of empathy and active listening, use of open-ended and priming questions, verification of patient understanding, overcoming of communication barriers, communication with difficult patients, communication with patients not interested in discussing smoking cessation and use of strategies to improve medication adherence.

Documentation was an important element of the workshop. The pharmacists were trained to document the patient’s smoking, medical and medication history, basic demographic characteristics, staging, assessment, education, counseling, follow-up and the personalized action plan to quit smoking. In addition, they were instructed on how to fill in the Fagerstrom test for nicotine dependence (FTND). The FTND is a six-item questionnaire designed to assist the healthcare professional in determining a patient’s degree of nicotine dependence [39]. This questionnaire has already been used in smoking-related research studies in the Middle East area [40,41]. Furthermore, they were instructed to measure the smoker’s health-related QoL using the Smoking Cessation Quality of Life (SCQOL) questionnaire. This instrument was developed and validated for use in smoking cessation [42,43] and has already been used in previous studies that tested the effectiveness of a pharmacist-delivered smoking cessation program [16]. This questionnaire tackles a total of 13 general and smoking cessation-specific quality-of-life domains including physical functioning, role-physical, bodily pain, general health, vitality, social functioning, role-emotional, mental health, social interactions, self-control, sleep, cognitive functioning and anxiety [43].

### Study/program marketing

The study pharmacists were trained to recognize many opportunities for the promotion of the smoking cessation program as possible. For example, when dispensing prescriptions, the study pharmacists were encouraged to ask patients about smoking and to tell them about the smoking cessation program. In addition, study site pharmacists displayed posters and leaflets in their pharmacy describing the smoking cessation program. Furthermore, the general practitioners and dentists practicing in the study ambulatory clinics were sent letters inviting them to refer their patients who are interested in quitting to the study pharmacies.

### Screening and eligibility criteria

Interested smokers meet with the study pharmacists. The study pharmacists use a scripted questionnaire to screen smokers in order to assess their eligibility for the study. Eligible participants are patients aged 18 years and older who currently smoke one or more cigarettes daily for 7 days, are motivated to quit, i.e., in the preparation stage of the stage-of-change model, able to communicate in Arabic or English, and are willing to and capable of attending the scheduled sessions at the study pharmacies. The motivation to quit is determined by the pharmacist using the transtheoretical model of behavior change [44]. Smokers in the precontemplation or contemplation stages are advised to quit, are provided with educational materials regarding tobacco cessation and the health benefits of quitting, and are encouraged to come back to the pharmacy when they feel they are ready to commit to quitting smoking.

Exclusion criteria are (1) use of other nicotine or tobacco products and (2) current use or use in the last 30 days of smoking cessation aids or medications, (3) planning to leave Qatar in the next 12 months, (4) presence of any major medical condition that would prevent use of the nicotine replacement therapy including hypersensitivity to the products, history of or recent myocardial infarction, life-threatening arrhythmias, severe or worsening angina, uncontrolled hypertension and temporomandibular joint disease (in case of nicotine gum), (5) pregnancy and (6) psychiatric illness or another debilitating condition that would interfere with participation in the study.

### Study enrollment

Following the completion of the screening procedure, the study pharmacist gives the eligible participant pertinent background information on the program, explaining what his or her participation would involve (including potential benefits, risks, inconveniences, discomforts), and his or her right to confidentiality. In order to enroll in the study, the interested participant is asked to sign an approved consent form. Once the consent form is signed, the pharmacist collects the participant’s contact information and sets an appointment with him or her at a date and time that is suitable for both of them.

### Initial appointment and randomization

One to two days before his or her scheduled appointment, the study pharmacist contacts the enrolled participant to remind him or her about the appointment. At this initial appointment, which takes around 30 min, the study pharmacist first collects the participant’s sociodemographic characteristics, current medical problems and medications, smoking history (i.e., number of cigarettes per day, duration of smoking, previous quit attempts, smoking habits of other family members and the participant’s reasons for wanting to quit smoking) and vital signs (i.e., blood pressure and pulse). In addition, the pharmacist assesses the smoker’s level of nicotine dependence using the Fagerstrom Test for Nicotine Dependence and measures his or her baseline exhaled carbon monoxide (CO) level using the exhaled CO test. Furthermore, the pharmacist administers the smoking cessation quality-of-life (SCQOL) questionnaires. After baseline data collection, the smoker is randomly assigned to either the intervention group or the control group. Randomization is already anonymously preset by the study statistician for each study pharmacist. According to the participant number and the preset list, the participant will be randomized to the intervention or control group. A new appointment is set with the participants assigned to the intervention group. Participants assigned to the control group receive brief unstructured smoking cessation advice as outlined below. Participants in both groups do not pay for their participation.

### Intervention group

Participants assigned to the treatment group participate in a face-to-face four-session program at the pharmacy delivered by the study pharmacist at 2-4-week intervals over 8 weeks. The sessions are set at a date and time that are convenient for both the pharmacist and participant.

#### First session

The first session is time-intensive, taking around 30 min. In this session, the study pharmacist facilitates the participant’s preparation to quit. The participant selects a quit date within the next 2-4 weeks. Based on the transtheoretical model of change, this would give him or her time to get prepared to enter the action stage on the quit date.

The pharmacist discusses the benefits of smoking cessation with the participant and provides him or her with tailored behavioral and lifestyle strategies. These strategies take into consideration the participant behaviors, values and beliefs. For example, if the smoker states that the hardest time would be at work when others are taking breaks to smoke, the pharmacist may suggest ways to spend the time during breaks. As outlined under the training section, the pharmacist also provides the participant with information about what to expect during the quit attempt with suggestions to cope with the early days of quitting. In addition, the pharmacist encourages the participant to seek family support during the attempt.

To prevent nicotine withdrawal symptoms, the participant is also offered, without cost, nicotine replacement therapy (NRT) as a patch or lozenge depending on his or her previous experience, preference and adverse effect profile. Other NRT dosage forms, e.g., an inhaler, nasal spray and sublingual tablets, are not available in Qatar. The gum is usually not tolerated by patients. The participant is not offered the other smoking cessation aids, including bupropion and varenicline, as they require a prescription in order to be dispensed in Qatar. Before dispensing the NRT, the study pharmacist ensures that the participant does not have any contraindications to nicotine therapy and is not taking any medication that would interact with NRT. The NRT is started on the participant’s intended quit date. Patient counseling about NRT is provided to each participant regarding the dosage, administration, scheduling, duration of therapy, adverse effects, interactions and proper disposal.

Participants who take the nicotine patch start at 21 mg if they smoke ten cigarettes or more per day. Otherwise, they receive a 14-mg patch. Both patches are continued for 6 weeks before being tapered. The 21-mg patch is decreased to 14 mg, continued for 2 weeks and decreased to 7 mg for a final 2 weeks. Patients who start with the 14-mg patch are tapered to 7 mg for a final 2 weeks [45]. Participants who take the nicotine lozenge use the 1-mg pieces. It is continued for 6 weeks as one lozenge every 1-2 h before being tapered. Then the participant takes one lozenge every 2-4 h for weeks 7 to 9, then one lozenge every 4-8 h for week 10-12 [46].

A personalized action plan is created by the pharmacist to document the participant’s quit date, nicotine replacement therapy dosage schedule and counseling, suggested behavioral and lifestyle strategies, and date/time of the next appointment. This plan is signed by both the participant and pharmacist.

#### Follow-up sessions

The first follow-up session is scheduled 1 week after of the participant’s quit day and takes around 20 min. In this session, the pharmacist determines the participant’s smoking status, measures his or her blood pressure/pulse/exhaled CO level, and assesses the NRT tolerability. If the patient succeeds in quitting, the pharmacist provides reinforcement and addresses problems associated with quitting such as managing withdrawal symptoms, coping with cravings, relieving stress, and managing fear of weight gain and of change in relationships with other smoking friends or relatives. If the participant fails to quit smoking, the pharmacist carefully reviews the participant’s experience during the attempt to quit and works through the identified problems. If the participant does not tolerate the NRT side effects (e.g., his or her blood pressure or heart rate increases), the pharmacist asks the participant to stop the NRT and refers him or her to the HMC smoking cessation clinic for further smoking cessation support. This participant is no longer enrolled in the study.

The second follow-up session is scheduled 2 weeks after the first follow-up session. The third follow-up session is set at 4 weeks after the second follow-up session. These sessions take no more than 10 or 15 min each. In these sessions the pharmacist assesses the participant’s smoking status, blood pressure/heart rate/exhaled CO level and NRT tolerability and provides NRT refills. In addition, he or she focuses on maintenance of smoking abstinence with cognitive-behavioral strategies to prevent relapse. The pharmacist documents any action taken by him/her at each follow-up session. After the third follow-up session, all participants are instructed to call or visit the pharmacy for questions or to receive additional support as needed. For more information on participant flow during the study, see Figure 1.

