**Participant flow during the study.**

#### Control group

Participants in the control group receive 5-10 min of unstructured brief smoking cessation counseling by the pharmacist (emulating current practice). In addition, they are provided with educational materials about smoking cessation and are offered nicotine replacement therapy (NRT). Before dispensing the NRT, the study pharmacist ensures that the participant does not have any contraindications to nicotine therapy and is not taking any medication that would interact with NRT. The choice of the NRT dosage form (patch or lozenge) depends on the participant’s previous experience, preference and adverse effect profile. The NRT dosage schedule and duration of therapy are similar to those in the intervention group. Control participants are not asked to attend any follow-up sessions.

The education materials address the following topics: the adverse effects of smoking, benefits of smoking cessation, the methods of quitting, setting the quit date, coping with nicotine withdrawal symptoms, getting emotional and social support, and monitoring the blood pressure and pulse when using NRT and avoiding relapse.

The study team invests a good deal of time orienting the study pharmacists on their role and training them on how to deal with the control and intervention groups. Part of that orientation is on how ‘not’ to provide any intervention to the control subset of smokers.

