### Data analysis

The CONSORT guidelines will be followed when analyzing the study data. Demographics and other variables related to smoking and quality of life will be summarized using frequency distributions (for categorical variables) and means with standard deviations (for numeric variables) and will be compared between the two study arms using the chi-squared test (or alternatively the Fisher’s exact test for small cell counts) for categorical variables and the independent *t*-test (or alternatively the Wilcoxon rank sum test for non-normally distributed variables) for numerical variables.

The main outcome will be continuous abstinence at 12 months as self-reported and verified by the CO test. The percentages of participants achieving the main outcome will be computed and compared between the two groups using the chi-squared test. Moreover, the difference in the proportions of continuous abstinence at 12 months between the two study arms (with 95% confidence intervals) will be computed along with the number needed to treat. Multiple logistic regression will be used to obtain the odds ratio of the main outcome between the two study arms adjusting for any imbalances in demographics or other baseline smoking-related variables. Moreover, mixed effects logistic regression, with pharmacy-level random effect, will be considered to adjust for the possible pharmacy effect if it existed. The intent-to-treat principal will be used in the analysis whereby participants who will be lost to follow-up will be classified as smokers and included in the main analysis. This includes those who were removed from the study because they could not tolerate NRT side effects. A sensitivity analysis following that of Borelli, Hogan et al. will be done where the outcome has three possible categories: abstinence, no abstinence and dropout [48]. The suggested multinomial model will allow assessing factors affecting abstinence as well as factors affecting dropout. This will aid in understanding who might need more support during the intervention. Similar analyses for the primary outcome will be done at 3 and 6 months (but do not include verification of abstinence using CO tests).

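### Participants who cannot tolerate NRT leave the study and are scored as smokers although their outcomes could still be collected, and this falls mainly or wholly on the intervention arm

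*Protocol article*

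**What the plan says.** All references are to the protocol article.

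- **Intervention group:** "Participants assigned to the treatment group participate in a face-to-face four-session program at the pharmacy".
- **Follow-up sessions:** at the first follow-up session, one week after the quit day, the pharmacist "measures his or her blood pressure/pulse/exhaled CO level, and assesses the NRT tolerability". The second and third sessions repeat the check: "In these sessions the pharmacist assesses the participant’s smoking status, blood pressure/heart rate/exhaled CO level and NRT tolerability and provides NRT refills". A participant who does not tolerate NRT is asked to stop it and is referred to the hospital smoking cessation clinic. The section then states: "This participant is no longer enrolled in the study".
- **Control group:** NRT is offered here too: "The NRT dosage schedule and duration of therapy are similar to those in the intervention group". But "Control participants are not asked to attend any follow-up sessions", and no later tolerability check or removal rule is described for this arm.
- **Outcome measures:** research assistants blinded to allocation telephone both arms at 3, 6 and 12 months. Those reporting 7 days without smoking at 12 months are invited for a CO test.
- **Data analysis:** the main outcome is continuous abstinence at 12 months, self-reported and CO-verified. Under intent to treat, people lost to follow-up are classified as smokers, and "This includes those who were removed from the study because they could not tolerate NRT side effects".

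**The concern.** Scoring missing as smoking is a familiar convention for people who cannot be reached. Here it is extended to people who can be reached and whom the protocol itself removes. Their outcomes come from telephone calls that do not depend on the pharmacy sessions, so nothing in the outcome collection requires them to leave. Counting them in the denominator preserves the randomised groups, but a failure fixed by rule is not their outcome.

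The rule is also uneven. Both arms may use NRT, but the sessions that would reveal intolerance are scheduled in one arm only. A control participant with the same side effects is still called and can count as abstinent.

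At stake are the size of the treatment effect, the number needed to treat, the odds ratio and the cost per additional quitter. If removal ends the calls, which is the natural reading, quality-of-life and later cost data for these people are lost as well. The first tolerability check comes one week after the quit day, so almost the whole of follow-up can go.

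**Working it through.** **Inputs from the Sample size calculation section:** 12-month abstinence of 3% (control) and 15% (intervention), two-sided alpha 5%, power 90%, 118 per group.

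**Step 1: reproduce the plan's figure.** With the pooled two-proportion formula without continuity correction and mean rate 0.09:

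n = [1.96 × √(2 × 0.09 × 0.91) + 1.2816 × √(0.03 × 0.97 + 0.15 × 0.85)]² / 0.12² = (0.793 + 0.507)² / 0.0144 ≈ 117.4, rounded up to 118.

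This matches. Power at 118 per group is 90.1%.

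**Step 2: effect of the rule.** Let r be the share of the intervention arm removed for intolerance and q the share of those who would have been abstinent at 12 months. The observed intervention rate becomes 15% − r × q, and the control rate stays at 3%. The documents give neither r nor q. I assume r = 2%, 5% and 10%, and set q to the design rate of 15%.

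| r | r × q (points) | Intervention rate | Difference | NNT | Odds ratio | Power at 118 |
|---|---|---|---|---|---|---|
| 0 | 0 | 15.0% | 12.0 | 8.3 | 5.71 | 90.1% |
| 2% | 0.30 | 14.7% | 11.7 | 8.5 | 5.57 | 89.1% |
| 5% | 0.75 | 14.25% | 11.25 | 8.9 | 5.37 | 87.3% |
| 10% | 1.50 | 13.5% | 10.5 | 9.5 | 5.05 | 83.9% |

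The r = 10% row in full: the mean rate is 0.0825. The null standard error is √(2 × 0.0825 × 0.9175 / 118) = 0.0358. The alternative standard error is √((0.0291 + 0.1168) / 118) = 0.0352. Power = Φ[(0.105 − 1.96 × 0.0358) / 0.0352] = Φ(0.99) = 83.9%. In people, this is 118 × 0.10 = 11.8 removed, of whom 11.8 × 0.15 ≈ 1.8 abstainers are recorded as smokers.

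**Step 3: separate the scoring from the asymmetry.** Suppose the same rule removed 10% of both arms, and those removed would otherwise have had their own arm's design rate. The rates would be 15% × 0.9 = 13.5% and 3% × 0.9 = 2.7%, a difference of 10.8 points with power 86.5%. So 12.0 − 10.8 = 1.2 of the 1.5 points lost come from scoring removed people as failures at all, and 10.8 − 10.5 = 0.3 from the rule acting in one arm. At r = 5% the split is 0.60 and 0.15.

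**Limit of the arithmetic.** The 3% and 15% are 7-day point prevalence rates, whereas the main outcome is continuous abstinence. The power figures are therefore illustrative. The identity bias = r × q does not depend on that.

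**The case against.** The other side has good points, and several limit the finding.

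- **Direction and disclosure.** The rule works against the programme, so it cannot create a false claim of superiority. It is also stated in advance. Both points stand. Counting departure to another cessation service as failure could be defended as a composite outcome, but the protocol does not present it that way. It calls it intent to treat.
- **Unknown size.** No intolerance rate is given. Eligibility and pre-dispensing checks exclude people with contraindications, and NRT is offered, not required. The effect may be small.
- **A larger effect through the clinic's success rate.** A reader might set q at 40%, because the protocol says the referral clinic "has a smoking cessation success rate of 40"%. The documents do not support that. The figure comes with no definition, time point or denominator. The main outcome is continuous abstinence since the quit day, so anyone who has smoked since then cannot meet it, whatever the clinic later achieves.
- **Asymmetry as the main cause.** A reader might infer that the rule can operate in one arm only and that this is the main source of bias. The scoring sentence in Data analysis is not arm-specific, and control participants receive material on monitoring blood pressure and pulse, so one of them could report intolerance unprompted. What holds is that detection is scheduled in one arm only. Step 3 shows that the asymmetry is the smaller part.
- **Coding as dropout in the sensitivity analysis.** A reader might also infer that removed participants enter the three-category model as dropouts. Data analysis does not say how they are coded there. However they are coded, that model cannot recover outcomes that were never collected.
- **The remedy has its own imbalance.** Referral as described also arises from the intervention sessions, so observed outcomes could credit specialist help mainly to that arm. This stands, and the fix has to make it visible.

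**Conclusion.** The point holds as a real but probably modest flaw. The protocol gives up outcomes that it could collect and replaces them with fixed failures, mainly or wholly in the intervention arm. This understates the effect measures and, other things equal, overstates the cost per additional quitter. With 2-10% of the intervention arm removed and 15% of those otherwise abstinent, both assumed, the understatement is 0.3-1.5 points of the planned 12, and power is 89-84% instead of 90%. The bias is nil if no removed participant would be abstinent. It does not threaten a positive superiority result, but it can hide or shrink a true effect. It also rests on reading the end of enrolment as the end of follow-up, which the scoring rule supports but no sentence states outright.

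**What to change.** Reconcile Follow-up sessions with Data analysis by separating stopping NRT from leaving the study. The NRT stopping and referral rule itself is not questioned.

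1. In Follow-up sessions, replace the sentence that ends enrolment. State that the participant remains in the study for the 3-, 6- and 12-month calls and the 12-month CO test unless consent is withdrawn.
2. In Data analysis, delete the sentence that scores removed participants as smokers. Analyse their observed status in the arm to which they were randomised, and reserve missing = smoker for true loss to follow-up.
3. Record use of the referral clinic in both arms and report it by arm.
4. Keep the present scoring (NRT intolerance = smoker) as a sensitivity analysis, so that abstinence gained with outside help can be seen.

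The cost is a protocol amendment, a few more calls by research assistants already in post, and recontact of anyone already removed, possibly with renewed consent. Some outcomes will reflect help from the referral clinic, which items 3 and 4 expose but do not remove. Trial status says recruitment is ongoing, so the change is best made now: outcomes not collected cannot be restored at analysis.
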